### Data Handling

All data collected in the applied project were stored in the database on servers of the German Institute of Human Nutrition and backed up regularly. Applicant access to these databases is guaranteed. During the process of data collection, the study data were pseudonymized, and the identifying data were stored separately from the research data. After completion of data collection, the data were anonymized for the process of research. In accordance with the rules of good scientific practice, the anonymized data will be archived on servers of the German Institute of Human Nutrition infrastructure for at least 10 years.

## Results

The ChronoFast clinical trial is currently ongoing. The estimated primary completion date is December 2022. The trial aims to compare effects of eTRE and lTRE on insulin sensitivity, other cardiometabolic and inflammatory markers, and sleep quality when calorie deficits are minimized and body weight is nearly stable. Further objective is to elucidate molecular mechanisms underlying metabolic changes in adipose tissue and blood monocytes in women with overweight and obesity.

### Expected Findings

The study hypothesis is that both interventions will improve glycemic control, lipid metabolism, inflammation, and sleep quality because of reduced eating time while minimizing weight loss as effectively as possible. In detail, we expect an improvement in glucose tolerance, insulin sensitivity, and, possibly, beta-cell function, and a decrease in postprandial and daily mean glucose levels. Moreover, we expect that participants with impaired fasting glucose or impaired glucose tolerance will improve their glycemic status more effectively than people with normal glucose tolerance. We also expect a decline in blood pressure, blood triglycerides, total and LDL cholesterol, and possibly in sleep quality upon both eTRE and lTRE interventions. Furthermore, based on previous observations concerning meal timing and TRE, we hypothesize that the restriction of food intake at the beginning of the day (eTRE) will show more beneficial metabolic effects compared with the food intake restriction at the end of the day (lTRE), which might be associated with different molecular signatures in the fasting adipose tissue. We expect that genes and pathways involved in glucose and lipid metabolism, inflammation, oxidative stress, and autophagy, as well as clock genes, will be affected by meal timing. Finally, we suppose that eTRE vs. lTRE will shift the internal circadian time assessed by the BodyTime assay in opposite directions.

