## Materials and Methods

### Study Design

The study named “ChronoFast” is a 10 week randomized, controlled cross-over clinical trial that will be performed in a German population of female subjects with overweight or obesity. The study will consist of two 2 week dietary intervention periods: (1) early TRE and (2) late TRE. After a 4 week long run-in period, the participants will be randomly assigned to either 2 weeks of eTRE or 2 weeks of lTRE as their first intervention. The first phase of intervention will be separated by a 2 week washout period from the second phase of TRE intervention that will be the opposite of the first intervention (Figure 1). The duration of the run-in phase, and the washout and intervention phases were chosen to exclude the effect of monthly ovarian cycle in women (both intervention phases will be approximately at the same phase during both interventions). Previous data of our and other groups show that change in dietary pattern for 2 weeks is sufficient to induce strong changes in metabolic state (55, 58, 66). Furthermore, the short 2 week duration of TRE interventions will make the rigorous monitoring of food intake and physical activity more feasible and will allow for the achievement of minimal variation in body weight.

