Eating behavior will be assessed using a smartphone app or paper-based handwritten food diaries to determine the macronutrient composition, energy intakes, and timely compliance for 14 consecutive days during the run-in (baseline period) and each intervention. For these 14 days during each study period, the participants will be simultaneously fitted with a continuous glucose monitoring (CGM, FreeStyle Libre 2; Abbott, Chicago, IL, USA) device to measure interstitial glucose, whereas activity and sleep patterns will be tracked by an accelerometer (ActiGraph wGT3X-BT; ActiGraph, Pensacola, FL, USA) (Figure 1). Furthermore, the participants will be advised to maintain their habitual sleep–wake routine over the course of the study and complete sleep diaries and weight protocols for 14 days during the run-in phase and both intervention periods. On the last day of both intervention periods, the subjects will also complete the Visual Analog Scale to assess satiety and hunger scores.

The study includes a screening examination before the run-in phase and four visits before and after each intervention periods (Figure 1). On these days, the participants will visit the examination center for anthropometric measurements (body weight and composition, waist and hip circumferences), assessment of blood pressure, collection of fasting blood samples for routine laboratory tests, and metabolic biomarker analysis as well as a 3-h oral glucose tolerance test (OGTT) for the additional assessment of glycemic control (Figure 1). At visits 2 and 4, subcutaneous adipose tissue (SAT) samples will be additionally collected. A detailed overview of visits and assessments is shown in Table 1.

**Table 1 T1:** Overview of visits and assessments.

**Method/procedure**	**Main parameters**	**Pre-screening (phone, mail)**	**Screening**	**Visit 1**	**Visit 2**	**Visit 3**	**Visit 4**
Week			0	4	6	8	10
Inclusion/exclusion criteria		•	•				
Chronotype questionnaires: MCTQ, MEQ	Chronotype	•					
Physical examination			•				
Informed consent			•				
Randomization			•				
Anthropometric measurements	Body weight, waist and hip circumferences		•	•	•	•	•
Bioelectrical impedance analysis (BIA)	Fat and lean mass and percentage		•	•	•	•	•
Blood pressure measurement	Blood pressure		•	•	•	•	•
Fasting blood sample	Clinical biochemistry, other metabolic and inflammatory biomarkers		•	•	•	•	•
Oral glucose tolerance test	Glucose, insulin, GIP, GLP-1		•	•	•	•	•

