### eTRE and lTRE Interventions

Before and after each intervention period (eTRE and lTRE), the participants visited the examination center where anthropometrical measurements, fasting blood sampling, and OGTT were performed after overnight fast, and PSQI sleep questionnaire were completed (visits 1–4, Figure 1). Subcutaneous adipose tissue (SAT) biopsies were taken after both intervention periods (visits 2 and 4). At visits 1 and 3, the CGM sensor and ActiGraph were fixed on the body, and nutritional consulting was performed by the dietician who explained eating behavior during the TRE intervention.

The participants were instructed to consume their habitual food between 8:00 and 16:00 h during the early TRE intervention phase and between 13:00 and 21:00 h during the late TRE intervention period to achieve a daily eating window of 8 h and fasting window of 16 h (Figure 1). The subjects were asked to consume their usual kind and amount of food within the 8 h eating window but were free to divide their food intake into as many meals or snacks as desired. For guidance, the participants received a copy of their individual food records and daily caloric intakes made in the run-in phase. Outside the eating window, the participants were allowed to consume water and non-caloric drinks e.g., tea and black coffee without sugar and milk, and, in limited amounts, very low-caloric diet sodas, mints, or chewing gum with sweeteners as a tool that may increase compliance. Telephone calls in the middle of each intervention and the run-in phase (7 days after visiting the examination center) were conducted in order to promote adherence to the assigned program and answer questions. Again, for the 14 consecutive days of the TRE intervention, the subjects documented eating behavior, wore the CGM sensor and ActiGraph device, and completed sleep diaries and weight protocols (Figure 1; Table 1).

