#### Subcutaneous Adipose Tissue Biopsies and Blood Monocyte Collection

Subcutaneous adipose tissue biopsies were collected at visits 2 and 4 at the level of the umbilicus using a well-established technique (72). The skin was anesthetized with 1% lidocaine. A small incision was made, and 1 g of adipose tissue was removed under sterile conditions using a cutting needle biopsy handy (14 G Somatex™, Germany). SAT biopsies were collected immediately before OGTT and frozen in liquid nitrogen until further analyses. An RNA-Seq analysis of the SAT samples was performed to elucidate and compare signaling pathways affected in the adipose tissue by eTRE and lTRE and validated by quantitative real-time PCR.

Peripheral blood mononuclear cells were isolated from fasting EDTA blood using BD Vacutainer® CPTTM with an integrated FICOLL™-gradient (BD Biosciences, East Rutherford, NJ, USA). Blood monocytes were isolated from the peripheral blood mononuclear cell (PBMC) samples using whole-blood CD14 microbeads (Miltenyi Biotec, North Rhine-Westphalia, Germany) as described (73). The PBMC and monocyte samples were stored at −80°C until the analysis of inflammatory gene expression and BodyTime assay for the determination of TRE effects on internal circadian time (74).

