The cross-over design is another very essential strength of the ChronoFast trial protocol, which will allow for the comparison of cardiometabolic effects of eTRE vs. lTRE directly in the same study subjects. Until now, only one cross-over trial that compared the effects of eTRE and lTRE has been published (58), which was accompanied by manifested weight loss after both interventions and, possibly due to this reason, observed no difference in the improvement of glucose and lipid levels between two dietary patterns. Notably, the 10 week study in the United Kingdom, which also aims to compare the metabolic effects of eTRE and lTRE on adults with increased type 2 diabetes risk, is currently ongoing (82). However, this study uses a three-arm parallel study design, whereas the ChronoFast study has a cross-over design, which removes variability between participants because each study subject acts as his own control.

Notably, a range of published TRE studies was conducted only with male participants, especially when time frames are short, as female participants tend to show cyclic changes in body weight and behavior owing to the female cycle. Thus, working with solely female participants is also a strength of this study. Because of the 4 week run-in phase and the detailed recording of baseline characteristics before each intervention, confounding factors will be eliminated.

The last objective of the ChronoFast study is assessment and comparison of molecular mechanisms induced by eTRE and lTRE in adipose tissue and blood monocytes. Numerous molecular mechanisms underlying the metabolic effects of TRE are intensively investigated in animal studies (45, 46, 83). Postprandial increase in various nutrients, such as glucose, lipids, and amino acids, affects both glucose and lipid metabolism and circadian clock pathways *via* key intracellular metabolic sensors such as SIRT1, mTOR, S6K, AMPK, PPARs, RORs, and Rev-Erbs (84). Notably, insulin (and possibly other meal-induced hormones) can directly entrain the circadian clock in liver and adipose tissue and in this way additionally affect metabolic outcomes (85, 86). The elegant study of Mukherji et al. (83) confirmed a central role of PPARα, Rev-Erbα, and CREB in circadian and metabolic changes induced by shifting of feeding time. However, most of these mechanisms were described in rodents and require intensive investigation in clinical settings to prove feasibility, safety, and effectiveness.

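### The hypothesis that both regimens improve outcomes has no habitual-eating comparator, and for OGTT measures the pre-post change cannot be separated from a biopsy taken just before the post-intervention test

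*Protocol article*

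**What the plan says.** The Expected Findings section states the hypothesis causally and for both regimens: "The study hypothesis is that both interventions will improve glycemic control, lipid metabolism, inflammation, and sleep quality because of reduced eating time". It adds that women with impaired fasting glucose or impaired glucose tolerance should improve more than those with normal tolerance, and only later that eTRE should do better than lTRE.

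Under Study Design, "The study will consist of two 2 week dietary intervention periods: (1) early TRE and (2) late TRE". Habitual eating occurs only in the run-in and the washout, neither of which is randomised against TRE. The phase lengths are justified by the ovarian cycle, so that "both intervention phases will be approximately at the same phase during both interventions".

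The OGTT is done at screening and at visits 1 to 4 and yields the primary outcome, the Matsuda index. Table 1 marks the adipose biopsy at visits 2 and 4 only. The biopsy section describes local anaesthetic, an incision and removal of 1 g of tissue, and says: "SAT biopsies were collected immediately before OGTT and frozen in liquid nitrogen until further analyses".

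The Discussion credits the run-in and the baseline recording before each intervention with the result that "confounding factors will be eliminated". Its limitations paragraphs cover sampling at a single circadian time. They do not mention the missing comparator, the biopsy or the pre-post cycle gap.

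**The concern.** A statement that both regimens work because the eating window is shorter is a comparison with habitual eating. The randomised contrast cannot answer it: if both regimens worked equally well, eTRE against lTRE would show no difference. The claim therefore rests on changes from V1 to V2 and from V3 to V4, or from the run-in for the wearable and diary measures.

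Those changes have no concurrent control. For the OGTT they also differ systematically in a procedure, because every post-intervention test follows a biopsy and no earlier test does. A change in the Matsuda index, or the absence of one, could then be credited to meal timing when the design cannot tell the two apart. A reader who relies on the Discussion would believe that this had been ruled out.

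**Working it through.** **Visit layout.** Weeks are from Table 1, biopsy timing from the biopsy section, and OGTT visits from the OGTT section. Cycle position is (week × 7) modulo 28, counted from each woman's own screening day.

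| Visit | Week | On TRE | Relative cycle day | Biopsy before OGTT |
|---|---|---|---|---|
| Screening | 0 | 0 | 0 | 0 |
| V1 | 4 | 0 | 0 | 0 |
| V2 | 6 | 1 | 14 | 1 |
| V3 | 8 | 0 | 0 | 0 |
| V4 | 10 | 1 | 14 | 1 |

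**Biopsy.** The on-TRE and biopsy columns are identical (0, 0, 1, 0, 1). Two of five OGTTs follow a biopsy, and both are post-intervention. No analysis of these visits can separate the two effects, and the second period only repeats the pattern. With an intercept, on-TRE, cycle half and biopsy as columns, the design matrix has rank 2 out of 4.

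**Cycle.** V1 to V3 and V2 to V4 are 28 days apart, so the design matches intervention with intervention. V1 to V2 and V3 to V4 are 14 days apart: 14/28 = 50% of a cycle. For cycles of 24 to 35 days the gap is 14/24 = 58% down to 14/35 = 40%. The phase matching therefore does not cover pre-post changes. The table counts days within one woman, however. No section ties screening or V1 to a cycle day, so women may start at different phases and their shifts can run in opposite directions. In the group mean that is mainly noise. Eligible ages are 18 to 70, so some women may not be cycling at all.

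**Which outcomes are touched.**
- *Post-load OGTT values and Matsuda index:* no comparator, biopsy, half-cycle gap.
- *Fasting blood:* no comparator and half-cycle gap. The fasting sample is at −5 min, but whether it precedes the biopsy is not stated.
- *CGM, actigraphy and diaries:* weeks 0–2 against 4–6 and 8–10. These windows start on days 0, 28 and 56, the same nominal phase, and are recorded away from the biopsy. Only the missing comparator applies.
- *PSQI:* it asks about the previous two weeks, so the biopsy problem does not apply.

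**Size.** The plan's power figure serves as a check on the calculation. A two-sided paired t-test with n = 30, 29 degrees of freedom and noncentrality 0.53 × √30 = 2.90 has power 0.801, which agrees with the stated 80% (the plan does not state sidedness). The same formula gives the rejection rate of a pre-post test when TRE has no effect but post visits carry a systematic non-TRE shift of b SD of the paired difference (noncentrality b√30). The values of b are assumptions, since the documents give none.

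| b | b√30 | Probability of rejection |
|---|---|---|
| 0 | 0 | 0.05 |
| 0.1 | 0.55 | 0.08 |
| 0.2 | 1.10 | 0.19 |
| 0.3 | 1.64 | 0.36 |
| 0.5 | 2.74 | 0.75 |

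**The case against.** The stated aim in the Abstract, Introduction and Conclusions is eTRE against lTRE. Expected Findings also states that superiority hypothesis, and V2 against V4 is balanced on the biopsy. That stands: the randomised comparison is untouched, and the point concerns a secondary, non-randomised claim.

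The screening-to-V1 change gives four untreated weeks at the same nominal phase without a biopsy. It does inform drift and test repetition. It is not randomised or concurrent with TRE, and it cannot separate TRE from the biopsy.

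A reader might infer more than the documents support on several points:
- That the half-cycle gap is a fixed bias which sample size cannot reduce. This needs a common starting phase, which is nowhere stated.
- That the biopsy pushes results in a known direction. The documents give neither the existence, size nor direction of an effect, and a shift could mask improvement as easily as mimic it.
- That every pre-post outcome is affected. CGM, actigraphy and diary outcomes are not touched by the biopsy or the cycle gap.
- That the mixed model contains only an eTRE–lTRE contrast. The article lists its factors but not the levels of treatment or which visits enter, and may leave these to a fuller plan. No such plan could supply the missing comparator.

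**Conclusion.** The concern holds in this limited form. Improvement because of reduced eating time has no randomised or concurrent habitual-eating comparator for any outcome. For post-load OGTT measures, including the Matsuda index, the pre-post change is also fully aliased with the biopsy. The half-cycle gap is a further caveat for visit-based measures in cycling women and acts mainly as noise. The Discussion's claim that confounding is removed is wrong as written for these changes.

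The actual size of any distortion cannot be estimated from the documents. The rejection rates of 0.08 to 0.75 rest on assumed shifts of 0.1 to 0.5 SD and are illustrations only. The aliasing rests on the biopsy and OGTT being done as described. The point does not weaken the eTRE versus lTRE comparison, and within-arm p-values need not be barred if they are labelled for what they are.

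**What to change.** - State that the randomised eTRE versus lTRE comparison is the only basis for causal or confirmatory claims.
- In Expected Findings, label as uncontrolled and exploratory both the statement that the two regimens improve outcomes and the statement that women with impaired fasting glucose or impaired glucose tolerance improve more. Drop the causal attribution to reduced eating time.
- Report V1–V2 and V3–V4 OGTT changes with the biopsy and half-cycle caveats. For fasting markers, say whether the −5 min sample precedes the biopsy.
- In the Discussion, replace the assurance about confounding with this limitation.

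No visit, measurement or sample size changes. The cost is that the trial gives up a within-arm efficacy claim that its design cannot support.

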## Discussion

ChronoFast is the first randomized clinical trial in Germany directly comparing the cardiometabolic effects of eTRE vs. lTRE in a cohort of overweight and obese woman using a cross-over design. The study is based on previous research on metabolic effects of TRE interventions performed in different cohorts of metabolically healthy or ill subjects (41, 47–64). However, the protocol of the ChronoFast trial considerably extends previous study protocols using novel digital tools of chrononutritional monitoring (electronic food diary, 24 h CGM, and actigraphy) and by including a larger range of cardiometabolic and behavioral outcomes (glucose and lipid levels, metabolic hormones, adipokines and inflammatory biomarkers, blood pressure, satiety/hunger scores, sleep quality, social and economic decision behaviors, and gene expression in adipose tissue and blood cells). These tools and measures will advance the understanding of TRE-induced effects and their mechanisms compared with previous studies.

The most important strength of the ChronoFast study protocol is the careful control of timely compliance, dietary composition, calorie intake, and physical activity during the study. The aim is to achieve as minimal as possible calorie deficit or even stable body weight. As mentioned above, it is unknown whether beneficial metabolic effects of TRE result from the shortening of eating window or from the weight loss that accompanied most published TRE trials (41, 47–59). Nevertheless, four carefully controlled or short-term (4–5 days) TRE trials revealed beneficial metabolic effects without caloric restriction or weight loss (59–61, 81), suggesting that timing factor alone can improve metabolic state. Because study subjects tend to restrict caloric intake upon TRE, several tools will be used in the ChronoFast study to avoid weight loss during the intervention as established previously (21). First, participants will be informed about the importance of maintaining constant body weight for the whole duration of the study. Second, subjects will receive their individual food records and daily caloric intakes made in the run-in phase for guidance. Participants will be asked to document their food selection, consumed amount, and time of each meal daily. Third, they will be instructed to record their weight daily and report any weight fluctuation of ≥ 700 g on 2 consecutive days. The dietician will be trained to counteract weight losses quickly through changes in dietary plans. The dietician will contact study participants by telephone calls in the middle of each intervention and the run-in phase (7 days after visiting the examination center) to increase adherence to the assigned program and answer questions. The same tools will be used to ensure that the macronutrient distribution remains unchanged throughout the study, so that no change in dietary composition will interfere with the limitation of the eating time window or with different eating times. Furthermore, the documentation of the time of each meal, in combination with the monitoring of postprandial glucose excursions by CGM, will ensure the careful control of timely compliance during the intervention. Finally, physical activity will be monitored throughout whole intervention periods by actigraphy. Hence, we will be able to exclude that the observed effects of TRE were influenced by changes in physical activity behavior.

The cross-over design is another very essential strength of the ChronoFast trial protocol, which will allow for the comparison of cardiometabolic effects of eTRE vs. lTRE directly in the same study subjects. Until now, only one cross-over trial that compared the effects of eTRE and lTRE has been published (58), which was accompanied by manifested weight loss after both interventions and, possibly due to this reason, observed no difference in the improvement of glucose and lipid levels between two dietary patterns. Notably, the 10 week study in the United Kingdom, which also aims to compare the metabolic effects of eTRE and lTRE on adults with increased type 2 diabetes risk, is currently ongoing (82). However, this study uses a three-arm parallel study design, whereas the ChronoFast study has a cross-over design, which removes variability between participants because each study subject acts as his own control.

Notably, a range of published TRE studies was conducted only with male participants, especially when time frames are short, as female participants tend to show cyclic changes in body weight and behavior owing to the female cycle. Thus, working with solely female participants is also a strength of this study. Because of the 4 week run-in phase and the detailed recording of baseline characteristics before each intervention, confounding factors will be eliminated.

The last objective of the ChronoFast study is assessment and comparison of molecular mechanisms induced by eTRE and lTRE in adipose tissue and blood monocytes. Numerous molecular mechanisms underlying the metabolic effects of TRE are intensively investigated in animal studies (45, 46, 83). Postprandial increase in various nutrients, such as glucose, lipids, and amino acids, affects both glucose and lipid metabolism and circadian clock pathways *via* key intracellular metabolic sensors such as SIRT1, mTOR, S6K, AMPK, PPARs, RORs, and Rev-Erbs (84). Notably, insulin (and possibly other meal-induced hormones) can directly entrain the circadian clock in liver and adipose tissue and in this way additionally affect metabolic outcomes (85, 86). The elegant study of Mukherji et al. (83) confirmed a central role of PPARα, Rev-Erbα, and CREB in circadian and metabolic changes induced by shifting of feeding time. However, most of these mechanisms were described in rodents and require intensive investigation in clinical settings to prove feasibility, safety, and effectiveness.

As mentioned above, we expect that genes and pathways involved in glucose and lipid metabolism, inflammation, oxidative stress, and autophagy, as well as clock genes, will be affected by meal timing, so significant differences will be observed between eTRE and lTRE. However, and this is a main limitation of the trial, most data will only be collected at one circadian time point, i.e., in the morning after the overnight fast. Hence, these transcriptome data will represent a one-moment molecular signature in the fasting adipose tissue and cannot validate circadian transcriptional response to altered feeding schedules observed in rodents, for which multiple sampling over 24 h [or at least at several time points (73)] is necessarily. Indeed, for circadian regulated genes, expression changes observed at one circadian time point will not necessarily mean that there is improvement or worsening. Because food intake is a potent *zeitgeber*, observed gene expression change may be a result of a phase shift in the rhythmicity meaning that if the same test is done later in the day, there will be no differences or changes in the opposite direction. Nevertheless, the ChronoFast study will provide novel data on the TRE-dependent regulation of non-circadian transcriptome (which is expectedly a larger part of adipose tissue transcriptome) and, in this way, expand the very scarce knowledge of the regulation of adipose tissue by meal timing in humans. Interestingly, a recent study investigating subcutaneous adipose tissue samples taken at 6 hourly intervals over 24 h under highly controlled “constant routine” conditions, observed only ~2% transcripts exhibiting circadian expression profiles (87), although other tissues showed that 10–30% transcriptome is circadian. However, if the expression of known circadian output genes is changed, the transcriptome data have to be interpreted with caution.

The same limitation has to be considered for the analysis of strongly circadian regulated clinical outcomes. However, most metabolic measures planned in the protocol (such as glucose, insulin, and incretins) are relatively stable in the fasting state and are much stronger affected by the meal intake than by the endogenous circadian rhythm. Such endogenous circadian rhythms usually show a relatively small amplitude and could be observed mostly in carefully controlled constant routine experiments. Therefore, it cannot be expected that the timing of food intake on the day before will meaningfully affect metabolic parameters in the morning after the overnight fast because of the phase shift in rhythmicity.

